# Is a preoperative multidisciplinary team meeting (cost)effective to improve outcome for high-risk adult patients undergoing noncardiac surgery: the PREPARATION study—a multicenter stepped-wedge cluster randomized trial

**DOI:** 10.1186/s13063-023-07685-3

**Published:** 2023-10-11

**Keywords:** Preoperative multidisciplinary team, High-risk, Complications, Costs, Quality of life, Risk tools, Frailty, Mortality, Patient’s preferences, Serious adverse events, Stepped-wedge randomized cluster design, Cost-effectiveness, Health technology assessment

## Abstract

**Background:**

As a result of increased life expectancy and improved care for patients suffering from chronic disease, the number of patients with multimorbidity requiring surgical intervention is increasing. For complex surgical patients, it is essential to balance the potential benefits of surgical treatment against the risk of permanent loss of functional capacity and quality of life due to complications. European and US guidelines on perioperative care recommend preoperative multidisciplinary team (MDT) discussions for high-risk noncardiac surgical patients. However, the evidence underlying benefits from preoperative MDT meetings with all relevant perioperative specialties present is limited. The current study aims to investigate the effect of implementation of preoperative MDT discussions for high-risk patients undergoing noncardiac surgery on serious adverse events.

**Methods/design:**

PREPARATION is a stepped-wedge cluster randomized trial in 14 Dutch hospitals without currently established preoperative MDT meeting. The intervention, preoperative MDT meetings, will be implemented sequentially with seven blocks of 2 hospitals switching from control (preoperative screening as usual) to the intervention every 3 months. Each hospital will be randomized to one of seven blocks. We aim to include 1200 patients. The primary outcome is the incidence of serious adverse events at 6 months. Secondary outcomes include (cost)effectiveness, functional outcome, and quality of life for up to 12 months.

**Discussion:**

PREPARATION is the first study to assess the effectiveness of a preoperative MDT meeting for high-risk noncardiac surgical patients in the presence of an anesthesiologist. If the results suggest that preoperative MDT discussions for high-risk patients are (cost)-effective, the current study facilitates implementation of preoperative MDT meetings in clinical practice.

**Trial registration:**

ClinicalTrials.gov NCT05703230. Registered on 11/09/2022.

**Supplementary Information:**

The online version contains supplementary material available at 10.1186/s13063-023-07685-3.

## Introduction

As a result of increased life expectancy and improved care for patients with chronic diseases, the number of frail patients and patients with multimorbidity requiring surgical interventions is rising [1, 2]. Frail patients and patients with multimorbidity undergoing noncardiac surgery are at high risk for postoperative complications and hospital readmissions [3–7]. Surgical treatment is often performed with the dual goals of improving quality of life as well as survival. However, there is a crucial balance between the potential benefits of surgery and the risk of permanent loss of functional capacity and diminished quality of life from surgical complications. Patients may prioritize quality of life over receiving treatment to extend their survival, even if the treatment offered follows current guidelines [8]. For the individual medical specialist faced with these high-risk patients, it may be challenging to determine whether a technically feasible procedure is also in the patient’s best interest.

Multidisciplinary team meetings accommodate discussions between various specialists regarding optimal and individualized treatment plans. In several medical specialties, MDT meetings are recommended and already frequently established [9, 10]. Oncological MDT meetings, also known as “tumor boards,” have been widely studied, describing potential benefits on patient outcomes [11]. Many high-risk patients scheduled for noncardiac surgery, however, have not been discussed in a multidisciplinary team meeting. Additionally, tumor boards usually focus on technical aspects of the disease and the surgical procedure and may be hindered by an excessive caseload, time pressure, and lack of patient-specific information [12, 13]. Furthermore, the anesthesiologist with specific knowledge on perioperative risks and care, is often absent. A discussion of patient-specific benefits and risks of the planned surgery may therefore be lacking, limiting the potential positive effect of discipline-specific MDT meetings on patient outcome [14].

European and US guidelines on perioperative care recommend preoperative multidisciplinary discussion for high-risk noncardiac surgical patients [15–17]. However, the added value of preoperative MDT discussions is currently based on the consensus of expert opinion, registries, and small or retrospective studies [5, 18, 19]. A previous study where high-risk patients planned for noncardiac surgery were selected for preoperative MDT discussions by the anesthesiologist at the preoperative clinic, showed that 43% of high-risk patients did not undergo surgery after discussion in a preoperative MDT meeting [5]. Cancelation of surgery was related to either the multidisciplinary team consensus-based advice or the patient’s own decision after reconsidering the surgical harm-benefit ratio.

The primary aim of this stepped-wedge cluster randomized trial (SW-CRT) is to assess whether preoperative MDT discussions for high-risk patients undergoing noncardiac surgery lead to a decrease in serious adverse events (SAEs) after 6 months. Secondly, the current trial will assess the cost-effectiveness of implementing a preoperative MDT meeting for high-risk noncardiac surgical patients compared to current preoperative screening practices. Furthermore, we aim to assess the effect of preoperative MDT discussions on survival, quality of life, and functional outcome, as well as the patient’s decision regret [20]. In addition, the quality of decision-making in these MDT meetings and facilitators and barriers for implementing MDT meetings in clinical practice will be investigated.

## Methods

### Study setting

This multi-center stepped-wedge cluster randomized trial (NCT05703230—ClinicalTrials.gov), the PREPARATION study, will be conducted in 14 academic, teaching, and general hospitals in The Netherlands (Additional file 2). High-risk noncardiac surgical patients are identified at the preoperative anesthesia clinic in each hospital. The intervention (MDT meeting including anesthesiologic expertise) will be implemented sequentially to 14 hospitals (clusters) without such an MDT meeting already established. This trial protocol uses the Standard Protocol Items: Recommendations for Interventional Trials (SPIRIT) reporting guidance [21]. The WHO dataset on this study is available as Additional file 3.

### Study population

Anesthesiologists screen all patients scheduled for noncardiac surgery in the participating hospitals to identify those eligible for participation in this trial. Patients are eligible if they meet the following inclusion criteria: ≥ 18 years of ageAmerican Society of Anesthesiology (ASA) physical status score ≥ 3Clinical Frailty Scale ≥ 4 [22]Planned for elective or semi-elective non-cardiac surgeryAs stated by the 2010 Dutch preoperative guideline [23]:
∘ Doubt by the surgeon, anesthesiologist or patient regarding the harm-benefit ratio of the surgical procedure∘ Doubt if the correct measures were taken to limit the perioperative risk as much as possible∘ Doubt if the patient agrees with the surgical and anesthetic plan and the expected risks

The exclusion criteria are:No informed consentEmergency surgeryThe impossibility to communicate with the patient directly or through a third party, such as a relative or an interpreterProposed surgical procedure for which a preoperative MDT meeting, similar to the current study intervention, already exists in that hospital at the start of the study

### Intervention

The intervention consists of implementation of preoperative MDT discussions for high-risk noncardiac surgical patients. In the preoperative MDT meeting, a patient is discussed among at least a surgeon, an anesthesiologist, and one or more medical consultant(s) and/or specialized nurses. Relevant medical consultants can be invited specifically based on the patient’s comorbidities. During the meeting, the attendees will review the technical aspects of the scheduled surgery, estimate the harm-benefit ratio of the procedure, evaluate the impact of existing comorbidities, and discuss the patient’s expectations and preferences.

At least the following questions should be discussed:Is the proposed surgical intervention the most appropriate care for this patient and what are the alternative treatments?Is the harm-benefit ratio of the proposed surgical intervention acceptable for this patient?Should the patient’s condition be optimized before undergoing the proposed surgical intervention?

To facilitate the implementation of preoperative MDT meetings, a toolbox is provided to the participating hospitals to guide discussion with regard to health condition, patient preferences in life, and treatment options (Additional file 4). This toolbox aids in the development of a comprehensive treatment plan. In addition, the Outcome Prioritization Tool (OPT) will be used preoperatively to systematically collect information regarding patients’ goals and preferences in life [24].

### Outcome

The primary outcome is the incidence of serious adverse events (SAEs) [25] at 6 months, defined as Grade 3 or more on the Clavien-Dindo classification following surgical intervention [26]. In the case of non-surgical management, serious adverse events will be graded accordingly, such as events necessitating endoscopic or surgical intervention, single or multiple organ failure, or death [26].

Secondary outcomes (Table 1) include:Cost-effectiveness from a societal and healthcare perspective, resource use measured by a patient cost questionnaire and via hospital electronic health records, health-related quality of life measured with the EQ-5D-5L for the construction of quality-adjusted life years (QALYs) [27] Functional status of the patient, measured by the 12-item WHO Disability Assessment Schedule 2.0 (WHODAS 2.0) [28]Patients’ experienced quality of life assessed by the abbreviated World Health Organization Quality of Life (WHOQOL BREF) [29]Patients’ regret about the treatment decision measured by the Decision Regret Scale [20]SurvivalThe attendance and self-assessed performance of MDT meetings are evaluated using a form that assesses various aspects such as structure, duration, cases reviewed, attending healthcare staff, medical specialty, initial queries, and treatment choices.Quality of MDT meetings by observations of multidisciplinary team discussion and decision-making by an independent, non-participant observer, using the MDT-MODe of decision-making (MDT-MODe) in a subset of MDT meetings [30, 31]Delay between preoperative screening, preoperative MDT meeting, and the surgical procedureFacilitators and barriers to organize preoperative MDT meetings

**Table 1 Tab1:** Primary and secondary outcomes, data sources, and used instrument/source of information

Outcome	Type of data source	Instrument/source
Serious adverse events	Registration	EHR
Functional status	Questionnaire	WHODAS 2.0 [28]
Health-related quality of life	Questionnaire	EQ-5D-5L} [27]
Quality of life	Questionnaire	WHOQOL BREF [29]
Decision regret	Questionnaire	Decision Regret Scale [20]
MDT characteristics	Registration	CRF
Perioperative management	Registration	CRF
MDT decision-making and facilitators and barriers	Observations and interviews	MDT-MODe [30]
Survival	Registration	EHR
Resource use	Questionnaire and registration	iMCQ and iPCQ: CRF: EHR [32]
Delay between preoperative screening, preoperative MDT, and surgery	Registration	CRF

*EHR* electronic health record, *WHODAS 2.0* World Health Organization Disability Assessment Schedule 2.0, *EQ-5D-5L* quality of life in 5 dimensions, *WHOQOL BREF* World Health Organization Quality of Life, short version, OPT Outcome Prioritization Tool, *CRF* case report form, *MDT-MODe* multidisciplinary team mode of decision-making, *iMCQ* iMTA (institute for Medical Technology Assessment) Medical Consumption Questionnaire, *iPCQ* iMTA Productivity Cost Questionnaire

### Design

The PREPARATION study is designed as a stepped-wedge cluster randomized trial and will be executed in 14 hospitals without a currently established preoperative MDT meeting for high-risk noncardiac surgical patients [33]. The current trial employed a stepped-wedge design to address ethical concerns. This decision was based on the appreciation for existing MDT meetings among patients and physicians and the moral dilemma posed by denying patients the opportunity to have their cases discussed in preoperative MDT meetings in hospitals where such meetings are already standard practice [4, 5, 34–36]. Therefore, participating hospitals were selected based on the absence of established preoperative MDT meetings. At the start of the trial, each participating hospital performs preoperative screening and management as usual without preoperative MDT discussions (phase 1). At the crossover time points, two study centers switch from the control condition to the implementation of preoperative MDT discussions (phase 2). After 24 months, all hospitals have implemented a preoperative MDT meeting (i.e., all hospitals will be exposed to the intervention).

The design pattern matrix (Fig. 1) illustrates the trial design. In total, there will be 7 blocks, each consisting of two hospitals. Each hospital will be randomized to one of the seven sequences prior to the start of the study by an independent person from the coordinating center (Fig. 1). The individual patient flow, either as a patient in phase 1 (control) or as a patient in phase 2 (intervention), is shown in Fig. 2. Computer-generated lists of random numbers will be used to randomly assign the hospitals to one of the sequences (2 hospitals per sequence/block) for the 7 fixed number of points in time of crossover (steps). Furthermore, we will stratify on the size of the hospital (small versus large). This ensures that the control and intervention are balanced on the type and size of the hospital. Each hospital will be informed of its own crossover date 3 months prior to this time point to ensure ample time for preparing the implementation of the MDT. All patients will be individually followed in time until 1 year from the day of surgery or the day of the preoperative MDT meeting in case of nonsurgical management.

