### Recruitment

Consecutive high-risk noncardiac surgical patients will be assessed for potential eligibility at the preoperative assessment by the anesthesiologist and asked to participate if they fulfill the inclusion criteria. Eligible patients will receive written and video information about the study. Written informed consent will be obtained by a trained (research) nurse or a physician before surgery (control; phase 1) or before the MDT meeting (intervention; phase 2). To facilitate the inclusion of patients with limited health literacy in our study, we incorporated measures to guarantee that information about the study, questionnaires, and informed consent were written at a suitable language level (level B1).

Each hospital is estimated to include ten patients on average per 3 months. As hospitals vary in size and do not serve the same number of surgical patients, each hospital includes a different number of patients during each period of 3 months. Patients can withdraw consent at any time for any reason if they wish to do so. Data from patients who withdraw will be used in the analysis until the date of withdrawal, unless the patient states otherwise.

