### Trial status

Protocol version: 2.5; October 18, 2022.

Trial start date: November 1st, 2022; Trial completion: November 1st, 2025.

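### Follow-up is anchored on surgery, or on the MDT meeting if there is no surgery: unoperated control patients have neither date, and the event window depends on a decision the intervention is meant to change

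*Protocol article*

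**What the plan says.** Four statements in the protocol article bear on this point.

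- **Design, follow-up.** One rule covers all patients, who are followed "until 1 year from the day of surgery or the day of the preoperative MDT meeting in case of nonsurgical management". No third anchor is given.
- **Design, control condition.** At the start, "each participating hospital performs preoperative screening and management as usual without preoperative MDT discussions (phase 1"). A control patient therefore has no MDT date.
- **Outcome.** "The primary outcome is the incidence of serious adverse events (SAEs) [25] at 6 months", and it is "defined as Grade 3 or more on the Clavien-Dindo classification following surgical intervention". For the others: "In the case of non-surgical management, serious adverse events will be graded accordingly". The start of the 6 months is not named, and the provision for non-surgical management is not limited to the intervention phase.
- **Statistical analysis plan.** The analysis follows intention to treat, so every enrolled patient needs an outcome window.

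Patients are enrolled before it is known whether they will have surgery. Consent is taken "before surgery (control; phase 1) or before the MDT meeting (intervention; phase 2"), according to Recruitment.

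**The concern.** An outcome measured at 6 months needs a start date that exists for every patient and is not itself moved by the treatment. The stated rule fails on both counts.

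First, it cannot be applied to an unoperated control patient. Such patients are foreseeable, because one set of eligibility criteria concerns doubt about the harm-benefit ratio, about risk-limiting measures, or about the patient's agreement with the plan.

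Second, for everyone else the anchor depends on whether and when surgery takes place. The article expects the MDT to change both. The Introduction cites an earlier study in which 43% of patients were not operated on after MDT discussion. The Intervention section requires the team to ask whether the patient should be optimised first. Delay to surgery is a listed secondary outcome.

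The primary comparison may then count events over differently placed windows in the two phases. Adjusting the mixed model for calendar period, hospital size or prognostic variables does not repair an outcome defined that way.

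**Working it through.** **Step 1. Does every patient have an anchor?** Applying the Design rule to the four possible groups:

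| Phase | Operated on | Not operated on |
|---|---|---|
| Control | day of surgery | none (no operation, no meeting) |
| Intervention | day of surgery | day of MDT meeting |

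One cell is empty.

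**Step 2. Which early events count?** Assume that the 6-month window uses the same anchor. This is an inference, but no other origin is stated and the Outcome definition ties events to surgery. Take a non-fatal SAE after enrolment and before any operation:

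- operated patient, either phase: not counted;
- unoperated intervention patient, event after the meeting: counted;
- unoperated control patient: no window to place it in.

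**Step 3. How many controls could be affected?** The plan's own total reproduces: 14 hospitals x 8 periods x 10 patients = 1120. With two hospitals crossing over at each of 7 steps, the sequences spend 1, 2, ..., 7 periods in control. That gives (1 + 2 + ... + 7) x 2 x 10 = 28 x 20 = 560 control patients, and 1120 - 560 = 560 intervention patients.

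The control cancellation rate u is not given, so it is varied. If unoperated controls were left out for want of a window, and their event rate were r against 43% in operated controls, the control rate would be overstated by u x (43 - r) points. Both u and r are assumptions. So is applying the Sample size section's 43% to operated controls.

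| u | controls without anchor (560 x u) | overstatement, r = 27.5% | overstatement, r = 10% |
|---|---|---|---|
| 5% | 28 | 0.78 | 1.65 |
| 10% | 56 | 1.55 | 3.30 |
| 20% | 112 | 3.10 | 6.60 |
| 30% | 168 | 4.65 | 9.90 |

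The planned difference is 43 - 27.5 = 15.5 points.

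**Step 4. Does the pre-surgery gap favour one phase?** Share of patients with an uncounted event = operated share x (1 - exp(-hazard x wait)). Assume a hazard of 2% per month for non-fatal SAEs that do not cancel surgery, 90% of controls operated on after 1 month, and 57% of intervention patients operated on (100% - 43%).

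- Control: 0.90 x (1 - exp(-0.02)) = 1.78 points.
- Intervention, wait 1 month: 0.57 x (1 - exp(-0.02)) = 1.13 points. Control loses 0.65 more.
- Intervention, wait 3 months: 0.57 x (1 - exp(-0.06)) = 3.32 points. Intervention loses 1.54 more.

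The sign changes with the assumed wait. Each phase's loss is an upper bound for a yes/no outcome, since some of these patients will also have a counted event later.

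**The case against.** The strongest reply is that the quoted sentence fixes only how long patients are followed, not when event counting begins. The patient-pathway and schedule figures are not shown, and the full protocol may hold a date for controls. It stands that the 6-month origin is an inference, and that no sentence says outright that pre-surgery events are discarded. But the article does more than leave a detail out: it states a rule for all patients that some controls cannot meet. A separate control anchor would fill the empty cell and still leave the window dependent on the decision to operate.

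A reader might infer more than the article supports:

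- **Pre-surgery deaths in intervention patients are lost, giving immortal time.** They are not. A patient who dies before surgery was never operated on, so the MDT date applies, and the Outcome section counts death under non-surgical management. Such deaths lack an anchor only in controls.
- **Costs carry the same bias.** The Economic evaluation expressly records the MDT discussion or standard screening among hospital resources.
- **The calendar cuts off the last patients.** Trial status reads "Trial start date: November 1st, 2022; Trial completion: November 1st, 2025", and 24 + 12 months uses all of it. But the Fig. 1 caption gives every patient 12 months of follow-up. A completion date that is weeks short is administrative and does not touch the 6-month outcome.

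**Conclusion.** The point holds in two parts. That unoperated control patients have no anchor follows directly from the Design section. That the 6-month window depends on the management decision follows if the primary outcome shares that anchor, which is the only origin the article offers.

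It would go too far to read this as a bias of known size or as one that favours the MDT. The control cancellation rate, the waiting times and the pre-surgery event rate are not given. Plausible values move the net effect of the uncounted pre-surgery events in either direction, and the figures for excluded controls rest on assumed rates and on one assumed way of handling them. They show only that the gap need not be negligible against the 15.5-point target. Because the primary outcome is affected, the definition should be settled before outcomes are analysed.

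**What to change.** For every patient in both phases, whatever the management, start the 6- and 12-month windows at the preoperative screening visit at which eligibility is assessed. Count all Clavien-Dindo grade 3 or higher (or equivalent) events and all deaths from that date. State that the planned index operation is not itself an event. Keep the surgery-anchored (or MDT-anchored) window as a sensitivity analysis, and say there how unoperated controls are handled.

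The screening date exists in both phases, precedes the decision, and is already needed for the delay outcome recorded on the case report form. Consent would not serve as well, because it is tied to a different later step in each phase.

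The costs are an amendment to the outcome definition and shifted dates for record extraction and questionnaires. Patients whose surgery is delayed also have less postoperative observation within the 6 months, which is why the present window is worth keeping as a sensitivity analysis. Enrolled patients must also have survived from screening to consent, so the length of that gap should be reported by phase.
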